# 1. OVERVIEW

## 1.1 Need for improvement

For people in acute mental health or addictions crisis, Alberta's emergency departments (EDs) are vital navigational and safety net hubs for assessment, treatment and referral to specialized services. In the past 3 years alone, the annual number of ED visits in Alberta has increased by 16% for children and youth seeking mental health and addictions care (from 10,977 visits to 12,702 visits). The greatest numbers of visits occur in Alberta's two children's hospitals—in 2017, EDs in the Alberta Children's Hospital and the Stollery Children's Hospital saw 2,406 and 2,397 visits, respectively, for mental health and/or addictions concerns. This study focuses on improving care in these two EDs and their connections to community-based follow-up after the ED visit.

Child and youth mental health and addictions crises vary. Common reasons for seeking ED care are suicidal intentions, panic attacks, illicit drug use, and aggressive behaviours that risk hurting others. For children, youth and their families, these crises are stressful, can be overwhelming, and leave the family vulnerable. In response, acute care must be specialized and multidisciplinary. To be more than a temporary patch, this care must also integrate with broader services such as primary healthcare and community- and school-based services. Current clinical care and health system gaps in Alberta, however, prevent many children and youth from receiving specialized and integrated care.

## 1.2 Overview of our innovation

Our team has co-designed with patient partners an **acute mental healthcare bundle** that combines well-vetted solutions to improve healthcare quality, efficiency, and equality. In this study, we will implement and evaluate these solutions together for the first time, to achieve system-wide transformation and improved patient-level outcomes.

**The acute mental healthcare bundle brings together multiple evidence-based assessment tools.** We bundle tools that are used in isolation in other emergency care settings—Ask Suicide-Screening Questions and HEADS-ED—in consultation with their developers. Together, these tools ensure comprehensive, efficient, high-value ED-based assessment that is family-centred.

**The bundle removes barriers to assessment and builds connections to care.** The bundle shifts crisis assessment from an ED physician to a mental healthcare provider, introduces direct access to follow-up care, and strengthens sharing of information between care services.

**The bundle introduces a shared decision-making framework for family engagement.** For our bundle to be more than a temporary patch, we introduce Choice from the Choice and Partnership Approach (CAPA) to urgent care clinics. CAPA has been implemented in diverse mental health services, cultures, and healthcare systems. Improvements include increased family engagement in the healthcare system, reduced wait times to service, high satisfaction with care, and reduced ED use.

To determine the bundle's impact on children/youth, their families, and the healthcare system, the objectives of this study are to determine if the bundle:

1. **Improves child/youth wellbeing** (measured using the Stirling Children's/Warwick-Edinburgh Mental Wellbeing Scales)
2. **Improves child/youth and family satisfaction with care** (measured using the Service Satisfaction Scale)

3. **Improves family functioning** (measured using the Beach Center Family Quality of Life Scale)
4. **Improves healthcare delivery** (by measuring ED length of stay, access and time to follow-up care, ED revisits)
5. **Reduces and shifts costs**

## 2. INTERVENTION AND PROPOSED CHANGES TO CLINICAL CARE

The acute mental healthcare bundle builds on existing services and committed healthcare resources and investments. *Figure 1* on page 3 outlines how the bundle will be implemented.

### 2.1 Improvements to triage in the ED

In the bundle, triage nurses will use the Ask Suicide-Screening Questions. The ASQ tool is validated for pediatric ED patients and is used in many EDs across the US based on its ability to accurately screen for suicide risk among children and youth seeking care. Because healthcare providers differ in how they ask questions, and patient responses are influenced by how questions are posed, a standard approach to risk screening using a robust tool (i.e., the ASQ) identifies patients at risk more accurately. For triage nurses who feel ill-equipped about assess a child/youth's risk, the ASQ is an important tool. In hospitals that use the ASQ, staff report being very comfortable asking the questions. The tool requires minimal training. The goal of the screening is to identify children and youth who require further ED-based assessment to determine the actual level of risk.

The ASQ consists of four yes/no questions, takes 20 seconds to administer, and is available in 13 languages. A child/youth who answers, "Yes" to any question or refuses to answer one, is considered to be 'high risk'. Such children/youth have a threefold high risk for suicide. Children who reply "No" to all questions are considered to be 'low-risk'.

**At Alberta Children's Hospital**, children and youth who screen low-risk on the ASQ will be given a **booked appointment within 24-48 hours at an urgent care clinic** (a partnered mental healthcare clinic located nearby that permits real-time scheduling by ED staff). This approach will ensure families can discuss their needs and concerns—this currently does not occur for low-risk concerns. Families will meet with a nurse or social worker to review the details of their appointment (e.g., date, time, location, and name of clinic staff), and will leave the ED within 30 minutes of arrival.

**At Stollery Children's Hospital**, children and youth who screen low-risk on the ASQ will be able to go to the co-located mental health clinic (located in the hospital) during the clinic's hours. During off-hours, these children and youth will be given a **booked appointment within 24-48 hours at an urgent care clinic** (a partnered mental healthcare clinic located nearby that permits real-time scheduling by ED staff).

ACUTE MENTAL HEALTH BUNDLE **EMERGENCY DEPARTMENT**

[figure not shown]

Figure 1. Care bundle implementation

## 2.2 Improvements to ED care

In the acute mental healthcare bundle, children and youth who screen high-risk on the ASQ **will not undergo medical clearance**. They will directly see a mental healthcare provider (e.g., psychiatric nurse, social worker) for a focused mental health assessment using the HEADS-ED tool.

The HEADS-ED mnemonic (Home, Education, Activities/Peers, Drug/Alcohol, Suicidality, Emotions and Behaviour, Discharge Reasons) is recommended for ED-based assessments. It improves communication, expedites decision-making, and guides the use of healthcare resources. Using the tool requires minimal training, and on average, should focus the mental health assessment so that it takes ~20 minutes to complete.

The HEADS-ED tool generates a total score and *action level* for the child/youth's concerns by summing the scores in each area in the mnemonic: 0 (*no/minimal functional impairment and no need for action*), 1 (*moderate functional impairment and needs action but not immediate*), or 2 (*severe functional impairment/needs immediate action*).

A total sum score <8 or 'suicidality' score of 0 or 1 will result in a 24-48 hour follow-up appointment in an urgent care clinic. ED physicians will provide medical evaluation if a concern emerges during the assessment or at the request of the family. This approach to assessment is expected to expedite mental health assessment, reduce ED physician costs, shorten ED length of stay, and provide families with follow-up after the ED visit.

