### **3.4 Bundle inclusion criteria**

Children and youth eligible to receive the care bundle will be identified by nurses at triage. Eligible children/youth must be aged <18 years and have a mental health complaint in one of the following categories:

- a) Anxiety
- b) Bizarre behaviour
- c) Concern for patient’s welfare

- d) Deliberate self-harm
- e) Depression/suicidal
- f) Homicidal behaviour
- g) Insomnia
- h) Pediatric disruptive behaviour
- i) Situational crisis
- j) Violent behaviour

We will create a pathway for ED healthcare providers to refer to that will describe bundle eligibility criteria in detail. All bundle-eligible children/youth will be triaged, registered, have charts and contact sheets created, and receive care that follows the newly created bundle pathway (see Figure 1). Families opting to stay in the ED to be seen will have triage completed and will be seen as per regular triage priorities and will initially be seen by an ED physician with mental health consultation performed as indicated.

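### Section 2.2 lets a HEADS-ED total below 8 lead to a 24-48 hour clinic appointment even when suicidality has the top score, and the readable text names no same-visit step for that score

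*Protocol*

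**What the plan says.** Section 2.2 covers children and youth who screened high-risk on the ASQ at triage. Section 2.1 says of them: "Such children/youth have a threefold high risk for suicide". They skip medical clearance. "They will directly see a mental healthcare provider (e.g., psychiatric nurse, social worker) for a focused mental health assessment using the HEADS-ED tool".

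Each HEADS-ED area is scored 0, 1 or 2, and the areas are summed. A score of 2 means "severe functional impairment/needs immediate action". The disposition rule follows: "A total sum score <8 or 'suicidality' score of 0 or 1 will result in a 24-48 hour follow-up appointment" in an urgent care clinic. The next sentence reads: "ED physicians will provide medical evaluation if a concern emerges during the assessment or at the request of the family".

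Other sections bear on the same step:

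- Section 3.4 lists "e) Depression/suicidal" among the eligible complaints and says that care follows the pathway in Figure 1.
- Section 3.5 excludes significant intentional self-harm, psychosis, Form 10 holds and police arrivals. It also allows a switch to traditional ED care at any time if the patient, family or team wants it.
- Section 3.8 counts psychiatry consultations after HEADS-ED as a monthly process outcome, has records audited monthly, and counts suicide attempts and suicides within 1 month as balancing measures.

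**The concern.** The scale label and the routing rule do not fit together. The label says that a score of 2 calls for immediate action. The rule makes a low total sufficient for an appointment one to two days later, whatever the suicidality score. In effect the total can outweigh the one item that bears most directly on safety.

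The group is already selected for risk, and the exclusions do not remove suicidal presentations from it. Section 2.1 offers the same 24-48 hour appointment to ASQ low-risk children (at the Stollery site, outside clinic hours). So a high-risk child with the top suicidality score can have the same stated disposition as a child who answered no to every screening question.

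At stake is what staff do when they follow the written rule closely. Section 2.4 asks for high fidelity to the bundle in the maintenance phase, so an unwritten exception could be taken for a deviation. The audit and the 1-month counts would show a problem only after the child had left.

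**Working it through.** The protocol gives no figure to reproduce here. The check is to list every score pattern and apply the rule as worded.

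**Inputs (Section 2.2).** Seven areas are listed, each scored 0, 1 or 2. The clinic appointment follows if total < 8 **or** suicidality ≤ 1.

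**Patterns.** All patterns: 3^7 = 2187. With suicidality 2: 3^6 = 729.

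**Distribution of the other six areas.** The number of patterns giving each sum from 0 to 12 is the set of coefficients of (1 + x + x²)^6: 1, 6, 21, 50, 90, 126, 141, 126, 90, 50, 21, 6, 1 (sum 729).

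**Suicidality 2, total < 8.** The other six must sum to 5 or less:

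1 + 6 + 21 + 50 + 90 + 126 = **294 of 729**, with totals 2 to 7.

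The lowest case is suicidality 2 with every other area 0 (total 2).

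**The 294 by number of areas scored 2, suicidality included:**

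| Areas scored 2 | Count | Derivation |
|---|---|---|
| One | 63 | six others in {0,1}, sum ≤ 5: 64 − 1 |
| Two | 156 | 6 × (1 + 5 + 10 + 10) |
| Three | 75 | 15 × (1 + 4) |

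In 75 patterns, then, suicidality and two further areas all carry the top score and the rule still leads to the clinic.

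**Suicidality 2, total ≥ 8.** 729 − 294 = **435** patterns. The rule does not cover them, and the readable part of Section 2.2 gives them no disposition.

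**Effect of replacing 'or' with 'and'.**

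- Suicidality 0, others ≥ 8: 90 + 50 + 21 + 6 + 1 = 168.
- Suicidality 1, others ≥ 7: 126 + 168 = 294.
- Suicidality 0 or 1 with total ≥ 8: 168 + 294 = **462**.
- Routed to the clinic under 'or': 2187 − 435 = 1752. Under 'and': 1458 − 462 = 996.
- The 756 patterns lost are the 294 of concern plus these 462, which would have no stated disposition.

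**Sensitivity.** If only six areas are scored, 147 of 243 suicidality-2 patterns meet the clinic rule. The conclusion does not depend on the number of areas.

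**Is any same-visit step tied to the score?**

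| Provision | Trigger in the text |
|---|---|
| ED physician evaluation (2.2) | a concern emerging, or a family request; no score named |
| Switch to traditional care (3.5) | wish of patient, family or team |
| Psychiatry consultation (3.8) | none stated; counted as an outcome |
| PDSA cycles (2.4) | refine the bundle over time; no score-based step |

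None of the four names suicidality 2.

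**The case against.** The strongest objection is that Section 2.2 may be only a summary. Care follows Figure 1, which is not readable here. Section 2.2 does not even state what happens at a total of 8 or more with suicidality 2, and Section 3.8 counts psychiatry consultations, other recommendations and admissions, so further routes exist. Their triggers may be in the figure. This stands as a limit: nothing can be concluded about the whole pathway. It does not remove the point, because Section 2.2 states a rule that conflicts with its own scale label and would need to be aligned with the figure in any case.

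A reader might infer that the protocol sends children with the top suicidality score home without escalation. The text does not support that. It does not say that the appointment is the only action. A mental healthcare provider has assessed each child and can change the track at any time. A top suicidality score can also reasonably be read as a concern that obliges physician evaluation, although that evaluation is called medical and may be meant for physical problems. What remains is that this reading is left to the individual provider.

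A reader might also take 'or' for a slip. It is the exact complement of an escalation rule requiring both a total of 8 or more and suicidality 2, so it may well be intended.

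Finally, the choice of cut-off is partly clinical, and Section 1.2 says that the tools were bundled in consultation with their developers. That is a reason to leave the routing rule alone. It does not explain what the immediate action is for a child who scores 2.

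**Conclusion.** The point holds for the written rule in Section 2.2. A total below 8 is sufficient for the clinic appointment even when suicidality is 2, and no readable passage says that this score triggers a step during the visit. The existing safeguards are discretionary, not tied to the score, or act after departure.

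The size is known only in score patterns: 294 of 729, on the assumption that all seven listed areas are scored. It would be wrong to read this as about 40% of children with suicidality 2, since the patterns are not equally likely and the protocol gives no score distribution. The number of children affected is unknown.

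Confidence is moderate because Figure 1 may already contain the step. The correction is still worth making: the possible harm is grave and the change to the text is small.

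**What to change.** Keep the routing rule in Section 2.2 and make suicidality 2 an explicit trigger of the provision that follows it, for example:

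> *A suicidality score of 2, at any total, counts as a concern: before the child leaves the ED, the mental healthcare provider obtains ED physician evaluation or psychiatry consultation and documents the disposition.*

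Make Figure 1 agree. If Figure 1 already sets a step for this score, use that step in Section 2.2 instead. The phrase 'at any total' also covers the combination for which Section 2.2 now gives no disposition. Do not simply replace 'or' with 'and', for the reason shown by the 462 patterns above.

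The change is best settled before the maintenance phase, when Section 2.4 stops changes to the bundle.

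The cost is one sentence and a check of the figure, with no added patients. Some children with suicidality 2 who would not otherwise have had a second assessment will stay longer in the ED and use physician or psychiatry time. Where a physician does it, this returns part of the work that the bundle aims to move, since Section 1.2 says "The bundle shifts crisis assessment from an ED physician to a mental healthcare provider". How much cannot be estimated from the protocol. Both services are ones that the protocol already mentions.

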## 2.3 Improvements in transitions between healthcare sectors

Currently, there is no standard access to follow-up care and recommendations are often non-specific. The care bundle will introduce Choice from CAPA to urgent care clinics. CAPA is a system transformation model with the goal of improving the flow of mental healthcare delivery through shared decision-making with families. Urgent care clinic resources (i.e., human resources and space) are readily available to support this transformation. In the bundle, Choice will deliver *the right mental healthcare, with the right people, at the right place, at the right time for families*. On the whole, CAPA has been shown to increase family engagement, reduce wait times, result in high satisfaction with services, and reduce ED use. CAPA is grounded in demand/capacity theory and Lean to smooth service flow, creating better patient and staff experiences. Full booking and streamlining of referrals will facilitate 24-48 hour follow-up care in urgent care clinics for children and youth discharged from the ED.

Using CAPA, the follow-up appointment in the urgent clinic will be a *Choice* appointment. It will focus on: a) understanding the main concern(s) and the child/youth/family's strengths, and b) developing joint goal setting and treatment planning. The appointment will conclude with a joint decision on what resources and services best match the family's context, needs, and goals. A *Partnership* appointment (treatment) can be booked as required. This prioritizing of *choice* promotes partnerships between a range of services for families—primarily healthcare, school, social and community-based services. Unique needs and preferences (e.g., newly immigrated, LGBT2Q, financial) are considered, improving the family experience. During this project, as needed, urgent care clinic staff will expand on existing processes for care coordination between services to support interagency connections and seamless transitions. As a result, families will be directly connected to and not required to self-advocate to receive the care they need.

## 2.4 Phases of bundle implementation at the study sites

Operational team leads will actively manage bundle implementation including how PDSA cycles will be used to refine and improve bundle components, change management activities (Section 6), and communication (Section 4).

### *Pre-implementation phase*

Sites will begin with a 12-month period where there are no active, systematic, mental healthcare delivery innovations introduced. This phase will serve to provide the collection of baseline outcome measurements. During the last 2 months of this phase, a change management team at each site will follow Prosci®; a structured methodology with practical tools to support changes in healthcare practices. To help teams organize the phases of change during bundle implementation, we are using Normalization Process Theory. Each site will include a change management lead, change specialist, 6 project team members, and 4 site champions. ED and urgent care clinic managers, patient care managers, nurse educators, and senior leaders will also be involved. The change specialist will work with site champions on training plans and change management strategies, identifying how the care bundle will impact individuals. Strategies will be informed by identifying individual and organizational risks, barriers, and enablers, and supported by a change management communication plan. The change specialist will create change management process maps, champion roadmaps, coaching and training plans for frontline providers, and a resistance management plan. These tools will support implementation in the next 2 phases. The change specialist will also create an electronic database to track adoption issues and progress. Completed change management components will be integrated into the project plan before implementation and reviewed quarterly for responsiveness to individual/organizational needs.

### *Implementation phase*

This phase will last 5 months at each site. Sites will introduce the care bundle, applying a quality improvement (QI) approach through iterative PDSA cycles. The purposes of PDSA cycles are to: (a) learn as quickly as possible whether changes lead to desired improvements in different settings; and (b) make adjustments accordingly, increasing our ability to confidently deliver and sustain impacts. Integrated data management will offer real-time outcome monitoring. Cycles will optimize system performance and ensure structure to bundle testing. With PDSA cycles, our team will be able to quickly determine if changes lead to desired improvements and make adjustments to optimize performance. Each cycle will test a change aimed at bundle improvement: planning the change based on change theory and previously collected data (Plan), enacting the change (Do), examining change impact (Study), and identifying learning to inform next steps (Act). We will carry out multiple cycles and analyze data from each cycle to detect system improvement. As cycle example, we could test the impact on ED length of stay by removing medical clearance by the ED physician. After 1 week of measuring length of stay and obtaining staff and family feedback, the bundle would be modified to incorporate learning and then tested on a larger group of physicians before permanent implementation. By assessing the impact of changes in real time starting with small patient samples, we will address challenges, reduce unintended consequences, and maximize staff and family engagement. This cyclical approach will mitigate risks in implementing untested changes. Successful change management within a system will be supported by: a) demonstrating need for change, b) engaging staff impacted by implementing changes, and c) creating evidence of success and sustainability. Findings from each cycle will be documented to support local learning and transferability of learning across sites.

During PDSA cycles, we will track change management activities. At the completion of each cycle, the site-specific change management strategy will be reviewed and refined. We have organized special teams at each site to oversee the cycles and change management plan:

- **Operational team leads** helped develop critical aspects of our implementation plan and will manage bundle implementation.
- **Quality improvement leads** will ensure PDSA cycles follow organizational quality management processes. These leads will also guide how findings from PDSA cycles will be used to refine and improve operationalized components of the bundle.
- **Change specialists** will consult with healthcare providers, unit/patient care managers and site champions to identify how practices/processes are influenced over time. Resistance or lack of engagement will be explored and addressed via change management process maps, champion roadmaps, coaching and training plans for frontline providers, and a resistance management plan.

